## Methods

### Design and setting

This is a pre-post study with process evaluation. Routine service data will be collected for a 12-month period prior to the intervention (retrospective data) and for 6 months after the intervention (prospective data). A six-month period is planned for implementation, but the post-implementation period will commence sooner if the existing waiting list has been reduced to below a target threshold (Fig. 1).

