## Intervention

The intervention is the implementation of the 5-step STAT model as described in the STAT handbook [22].

Step 1 requires data to be gathered about the demand for service over the preceding year as well as the ‘supply’ or clinic capacity. The essential demand data will be the number of people referred, the number of referrals that are rejected or withdrawn prior to being provided with an appointment, and the number of people who failed to attend.

Step 2 involves use of the data to calculate the number of new patient appointments required weekly to keep up with demand, including a buffer of 15% to allow for appointments that will be unavailable due to routine factors such as staff leave. These calculations also allow for patients who fail to attend and are rescheduled, using additional appointments.

Annual data are worked into an equation as follows:
$$ \left\{\raisebox{1ex}{$\left(x-y+z\ \right)$}\!\left/ \!\raisebox{-1ex}{$52$}\right.\right\}\times 1.15= Required\ number\ of\ appointment\ slots/ week $$
$$ x= number\ of\ referrals\ received\ \mathrm{annually} $$
$$ y= number\ of\ referrals\ rejected\ or\ withdrawn\ annually $$
$$ z= number\ of\ people\  who\  fail\ \mathrm{t}o\  attend\ and\  are\  provided\ with\ a\  new\  appointment $$

Step 3 is the reduction or elimination of the backlog of people currently waiting. Previous STAT trials have used different strategies to achieve this [22] and a multi-factor strategy will be developed in consultation with epilepsy clinic staff and key stakeholders. It will be emphasised that this is one-off, and once the waitlist is at the target level, the STAT model is designed to maintain patient flow to ensure that the waitlist does not return. The backlog reduction strategy may include: auditing the waitlist to identify whether all people referred still require the service; putting on a finite number of extra clinics; or providing brief consultations by phone or telehealth. It is anticipated that this stage will take between 3 and 6 months. The aim will be to reduce wait time to a target number of weeks, to be determined by the researchers in consultation with key stakeholders from the epilepsy clinic.

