### Data analysis

Primary and secondary data from the pre and post-intervention cohorts will be compared using *t*-tests for continuous data (waiting time, number of appointments, scheduled appointments, missed appointments, emergency department presentation and hospital admission data, and changes in patient risk and/or management) or equivalent non-parametric tests as appropriate. Chi squared statistics will be used to compare nominal patient-level data for the two groups.

The mean number of days waited each month and number of people on the waiting list at sequential time points will be analysed using interrupted time series regression, following methods described by Bernal [23]. It is hypothesized that the intervention will show a 40% reduction in wait time and the impact model will be a level change (Fig. 2).

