**Fig. 2 Fig2:**
[figure not shown]
Interrupted time series regression - Hypothesised level change

Focus group data will be audio-recorded and transcribed verbatim. Analysis will follow an interpretive description approach [24–26]. Two researchers will independently analyse transcripts line by line and assign codes to text. Researchers will discuss codes and identify themes, and member checking will be conducted to ensure that researchers have correctly interpreted discussion.

Qualitative and quantitative data will be combined and organized for analysis consistent with recommendations for process evaluation of complex interventions [21] (Fig. 3). To evaluate the process, causal assumptions will be described as well as contextual factors that facilitate, or hinder implementation and adaptations made to accommodate the setting. Fidelity will be examined by assessing whether the intervention was implemented according to the principles of the STAT model, such as whether the calculated number of assessment and review appointments were booked in the implementation phase. Reach will be determined by calculating the impact on the lowest priority referrals and those who have waited the longest. Hypotheses about the mechanism of impact, or *how* the change in wait time occurred will be generated in the light of the qualitative and quantitative data.

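### The interrupted time series names only a level change, so it does not test whether the wait-list reduction lasts, and it can overstate the reduction if the list partly regrows

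*Protocol article*

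**What the plan says.** The Data analysis section applies interrupted time series regression to two series: "The mean number of days waited each month and number of people on the waiting list at sequential time points will be analysed" by that method. In one sentence it then hypothesises that wait time will fall by 40% and states that "the impact model will be a level change". The Fig. 2 caption repeats the choice: "Interrupted time series regression - Hypothesised level change". No other impact model, slope-change term or end-of-period estimate is named.

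Three other places bear on this.

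- **Intervention, Step 3.** The backlog is cleared once, by means such as a list audit, extra clinics or brief consultations. After that, "the STAT model is designed to maintain patient flow to ensure that the waitlist does not return".
- **Design and setting.** Implementation is planned for six months, but "the post-implementation period will commence sooner if the existing waiting list has been reduced to below a target threshold".
- **Discussion.** The authors hope for reductions that are sustainable.

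The pre period is 12 months and the post period six. The sample size paragraph expects up to 24 monthly observations. The article does not say how the implementation months enter the regression.

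**The concern.** A level-change model estimates one step and, if a trend is included, one slope common to the periods before and after. In this study the step in the list is partly built in: the backlog is cleared by a separate one-off effort, and the post period may open early once the list is below its threshold. What would show the appointment model itself at work is that the list stays down. That is a statement about the course of the list after the step, and the named model has no parameter for it.

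The omission also affects the step estimate. If the list rises again after clearance, the common slope tilts upward to accommodate the rise. The pre-implementation line is then projected too high into the post period, and the step comes out larger than the plain difference in means. The comparison of pre and post cohorts does not fill the gap, because it averages over the whole post period.

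At stake is whether a reader can tell a list that was cleared and held from one that was cleared and is filling up again.

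**Working it through.** **The plan's own figure.** The only numerical power claim is for the two-tailed t-test: N = 975, a 40% reduction from 72 days, SD 85, variability halved afterwards, power over 0.99. Splitting 975 by 12:6 months (an assumption) gives 650 and 325. The difference is 0.40 × 72 = 28.8 days. The standard error is √(85²/650 + 42.5²/325) = √(11.12 + 5.56) = 4.08, so the ratio is 28.8/4.08 = 7.05 and the claim reproduces. It does not bear on the time series, for which the article claims only moderate power.

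**Inputs for the list count.** From the protocol: 12 pre months, up to six implementation months, six post months, and a list of 600 to 700. Assumed: a flat pre list at 650, the full six-month implementation, linear regrowth of g per month and, for significance only, independent residuals with SD 25 (taken from the 600 to 700 range).

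**Model.** y = a + b·t + c·D, with t = 1–12 and 19–24 and D = 1 in the post period. Implementation months are excluded.

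- Within-period sums of squares of t are 143 (pre) and 17.5 (post).
- With a flat pre period, b = g × 17.5/(143 + 17.5) = 0.109 g.
- Mean times are 6.5 and 21.5, which are 15 apart, so c = (post mean − 650) − 15 b.
- The month-6 value exceeds the post mean by 2.5 g. The reported step therefore exceeds the month-6 gap by 2.5 g + 15 × 0.109 g ≈ 4.14 g. Of this, 2.5 g comes from averaging and about 1.64 g from the tilted slope.

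| Post list, months 1 to 6 | g | Plain difference | Reported step c | Gap at month 6 |
|---|---|---|---|---|
| 65 to 390 | 65 | -422.5 | -422.5 − 15 × 7.09 = -529 (81%) | -260 (40%) |
| 140 to 340 | 40 | -410 | -410 − 15 × 4.36 = -475 (73%) | -310 (48%) |
| 192 to 650 (limiting case) | 91.7 | -229 | -229 − 15 × 10.0 = -379 (58%) | 0 |

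In simulation the step for the first row is significant in every run.

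**Feasibility.** 975/18 ≈ 54 patients are seen a month, or 325 in six months. If inflow is about equal to that, as the stable list suggests, 65 to 390 is a gain of 325, about the most that six months of referrals could add with nobody seen. The first row is therefore an upper-end illustration. The error scales with g, so milder regrowth gives a proportionally smaller one: g = 20 gives about 4.14 × 20 = 83 patients.

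**Sensitivity to coding.** For 65 to 390, with a linear fall during implementation:

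- Level only, no trend, implementation excluded: about -422 (65%).
- 24 points, common trend, step at month 13: about -296 (46%).
- 24 points, common trend, step at month 19: about -2, essentially no effect.

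In the limiting case (list cleared to 100, then full refill), the step at month 13 gives -344, against -195 for a list that holds at 100. The refilling list looks better. With the step at month 19 the refill gives +154, an apparent increase.

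**Mean days waited.** With monthly SE 85/√54 = 11.6 days, a return to 72 days by month 6 from a start of 43.2, 20 or 10 is reported as -34%, -60% or -71%. It is significant in 25%, 53% and 63% of runs.

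**With a slope-change term.** For 65 to 390, implementation excluded, the model gives level -585 and slope change +65 a month. The month-6 effect is -585 + 5 × 65 = -260, which is correct. The level term on its own is still large and significant, so it must not be read alone.

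**The case against.** Several points on the other side stand.

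- A reader might infer that a list refilling completely within six months would be reported as a large success. The arithmetic of that limiting case is right, but from 100 it needs about 92 net additions a month against roughly 54 patients seen. Steps 2 and 4 also size new-patient slots to demand plus 15%. The documents support partial regrowth as the case to plan for.
- A reader might infer that the fault is a fixed property of the plan. It depends on the coding of the implementation months. With the step at month 19 it disappears or reverses, although that coding counts the clearance months as pre-intervention, which sits badly with the stated 12-month pre period.
- A reader might infer that both series fail alike. For mean days waited the false signal is unreliable.
- A reader might infer that durability is the primary question. Research question [i] asks about average wait time. Maintenance is the model's rationale and a hope in the Discussion.
- The level change is worded within a hypothesis, and prespecifying an impact model is good practice. Even so, it is the only model named.
- Regrowth would be visible descriptively, because list counts, longest waits and new referrals are tracked monthly after implementation. But the stated regression would not estimate it.

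A rule that requires a non-significant post slope would not be sound. Counts of a standing list are autocorrelated, and with a truly flat post list the ordinary least squares slope is falsely significant in about 16–25% of runs at AR(1) correlations of 0.5 to 0.8.

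**Conclusion.** The concern holds in a limited form. The named model does not test whether the reduction lasts. If the list regrows, a level-plus-common-trend fit without the implementation months overstates the remaining reduction by about four times the monthly regrowth. At the upper end that means 81% reported when 40% remains.

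This rests on a flat pre list of 650, linear regrowth and a six-month implementation. The significance rates also rest on independent residuals with SD 25; autocorrelation would lower those rates but not move the point estimates. The documents do not support saying that the plan as written would pass off a failed intervention as a success: coding is unstated, complete refill is out of line with the clinic's throughput, and mean days waited is much less affected. This is a cheap improvement, not a flaw that undermines the study.

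**What to change.** In the Data analysis section and Fig. 2:

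1. Specify a level and slope change model for both series.
2. State that the implementation months form a separate phase or are excluded.
3. Use standard errors that allow for autocorrelation.
4. Report, with 95% confidence intervals, the post-implementation slope and the difference from the projected pre-implementation line at the last post month.
5. Base any statement that the reduction was maintained on those two estimates, without a pass/fail rule on slope significance.
6. Keep the level-only model as a secondary analysis.

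The cost is a change of wording and one model term, on data already to be collected. The downside is one degree of freedom, a less precise step estimate, and a weakly estimated slope for mean days waited: with six post points, power is about 44% for a return from 43.2 to 72 days. For that series the interval will be wide and should be presented as such.

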**Fig. 2 Fig2:**
[figure not shown]
Interrupted time series regression - Hypothesised level change

Focus group data will be audio-recorded and transcribed verbatim. Analysis will follow an interpretive description approach [24–26]. Two researchers will independently analyse transcripts line by line and assign codes to text. Researchers will discuss codes and identify themes, and member checking will be conducted to ensure that researchers have correctly interpreted discussion.

Qualitative and quantitative data will be combined and organized for analysis consistent with recommendations for process evaluation of complex interventions [21] (Fig. 3). To evaluate the process, causal assumptions will be described as well as contextual factors that facilitate, or hinder implementation and adaptations made to accommodate the setting. Fidelity will be examined by assessing whether the intervention was implemented according to the principles of the STAT model, such as whether the calculated number of assessment and review appointments were booked in the implementation phase. Reach will be determined by calculating the impact on the lowest priority referrals and those who have waited the longest. Hypotheses about the mechanism of impact, or *how* the change in wait time occurred will be generated in the light of the qualitative and quantitative data.

**Fig. 3 Fig3:**
[figure not shown]
Process Evaluation. Data sources-1-Organisation’s data report, 2-Focus group with staff, 3-Research log, 4-Financial report, 5-Record of backlog reduction actions. Blue boxes are key components of process evaluation. Green boxes indicate intervention and outcomes

A sample size of *n* = 975 over the 18-month data collection period will be sufficient to detect a hypothesised reduction in waiting time of 40% with a power of over 0.99, with alpha set to 0.05, based on comparison of mean waiting time pre and post intervention using a two-tailed t-test for independent groups. This estimation is based on historical data for the participating clinic with a pre-intervention mean waiting time of 72 days (SD 85 days). The calculation also assumes a 50% reduction in variability in waiting time data, based on the results of previous STAT trials [6]. There is some uncertainty in power calculations for time series analysis [23, 27], but the proposed number of monthly observations (up to *n* = 24) is expected to be sufficient to provide moderate power given a strong intervention effect, minimal seasonal effects and even distribution of data points are expected [23, 27, 28].

### Discussion

This study will add to the evidence about reducing wait times by finding out if the STAT model of access and triage, previously shown to reduce wait times by 34% in community outpatients [6], can deliver similar results in a specialist medical outpatient clinic. This setting presents new challenges, including longer waiting lists, different funding structures and complex systems for bookings, billing and reporting. However, like its counterparts in community outpatients, this service has experienced relatively stable demand despite the existence of a large waiting list and it uses a combination of assessment and follow-up appointments creating options for flexibility in service delivery. These factors provide reason to believe that implementation of the STAT model could lead to sustainable reductions in waiting time for people seeking care from this epilepsy clinic.

A limitation of the study includes the single group, pre post design, which makes it difficult to control for confounding factors such as policy and staffing changes that could affect wait time during the study period. As a service level intervention, a cluster randomised controlled trial would be the ideal study design to provide rigorous evidence of effectiveness of the STAT model in outpatient clinics. However, given that there are questions over feasibility in this setting, a pre post study with a process evaluation will provide important insights into whether the STAT model can be applied in this setting before progressing to a more complex trial. The use of time-series analysis somewhat mitigates the limitations of a pre post design and can be seen as a strength of the study. The process evaluation is included to enhance interpretation of results and research translation, providing practical and pragmatic information to others seeking to replicate and potentially scale up the intervention.

If this study is found to be effective for reducing wait time and improving equitable access to the epilepsy clinic, then implementation of the STAT model may be applicable to other specialist medical outpatient clinics, and may have significant effects on patient outcomes [29]. At the health service where this study will be completed, a readily available report through the internal database indicates that the number of people waiting for all outpatient services is 37,810. This has additional implications in that outpatient waiting lists have also been described as hidden waiting lists for surgery [30]. More efficient, equitable and accessible delivery of outpatient services has the potential to affect thousands of people, improve health outcomes, prevent adverse events, and enhance patient flow across the health continuum.

## Data Availability

Non-identifiable data for the key outcomes will be available from the authors on request at the conclusion of the study.

## Abbreviation

STAT: Specific Timely Appointments for Triage
